## Methods

After receiving signed informed consent from the students for participation, we will carry out a randomized trial using a sample of 280 new undergraduate students at FES-Zaragoza, UNAM. The groups will be as follows. (i) An experimental group (n = 140) of 20 students will be made up from each of the seven departments (careers); these participants will receive training as “university student health promoters” through an e-learning course, in which the topics established for a UHP will be reviewed [21,22] (Table 1). (ii) The control group (n = 140) will consist of 20 students from each of the seven departments (careers), but they will undergo no training (Figure 1).

**Table 1 T1:** E-learning topics for the training of university health promoters

-My virtual classroom	-Body hygiene and health
-University student health determinants	-Safe and healthy environment
-How does my body work	-Addiction prevention
-Communication for health	-Conflict management
-Student leadership and health	-Recreation and health
-Health promotion: university health promoter	-Health and cultural activities
-Self-care	-Student support networks and health self-monitoring
-Healthy eating	-First Aid
-Physical activity and health	-University tutoring for health
-Self-esteem and health	-Ethics and health self-care

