### Sample size

For the calculation of sample size it was assumed a prevalence of 40% of overweight and obesity considering the results of the unpublished studies. We considered a significance level of 5%, a difference in clinical interest of 10% related to the control group, and a precision of 2.5% with a power of the 90%.

A healthy-lifestyle questionnaire will be given to all the participants, and the parameters will be detailed in the self-care card before and after the training (Additional file 1: Table S2 and Additional file 2: Table S3). The study variables will be as follows: (i) independent variable—compliance with the e-learning course for promoting health; (ii) dependent variables—lifestyles changes prior to the educative intervention (including healthy eating, physical activity, and addiction prevention) and parameters related to health status in self-care (including weight, body mass index, waist circumference, and hip circumference); and (iii) intervenient variables—age, gender, health status before training, current lifestyle (before training), family income, academic course, parents’ schooling, and parents’ health status. All dependent variables will be measured prior to and after the educative intervention.

Later, the students who comply satisfactorily with the e-learning course will replicate the course to 10 of their classmates. We are considering a follow-up every 6 and 12 months during 4 years.

Data will be processed using SPSS ver. 15.0 (SPSS, Inc., Chicago, IL, USA) statistical software. Descriptive statistics will be presented as means ± standard deviations. Results will be analyzed using Student’s *t* test and logistic regression analysis odds ratios with 95% confidence intervals. Pearson’s correlations will be obtained and *p* <0.05 will be considered significant. Analysis of the open answers will be conducted using ATLAS. ti 5.5 software.

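### The stated sample-size inputs, including 90% power, do not yield 280 students: 140 per arm gives about 42% two-sided power for 40% v 30%, and the 2.5% precision is undefined and unmatched

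*Protocol article*

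**What the plan says.** The Methods fix the size: "we will carry out a randomized trial using a sample of 280 new undergraduate students", split into 140 trained and 140 control students, 20 per arm from each of seven careers. The abstract repeats these numbers.

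The Sample size section gives the inputs but no resulting number:

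- Event rate: "For the calculation of sample size it was assumed a prevalence of 40% of overweight and obesity", taken from unpublished studies at the faculty.
- Significance: "We considered a significance level of 5" per cent. Whether the test is one- or two-sided is not stated.
- Effect, precision and power: "a difference in clinical interest of 10% related to the control group, and a precision of 2.5% with a power of the 90" per cent. Whether the 10% is absolute or relative is not stated, nor what the precision applies to.

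No standard deviation, baseline correlation or rate of discordant pairs is given.

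**The concern.** All the inputs of a standard two-proportion calculation are printed, and so is the size of the trial, so the one can be checked against the other. A ten-point difference from a 40% base rate with 90% power ordinarily needs several hundred people per arm, so 140 looked far too few. A margin of 2.5 points also looked too tight for 280 people.

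What is at stake is how the result is read. If the overweight/obesity comparison is not significant, a reader who relies on the stated 90% would take it as good evidence against an effect of the size the authors call clinically relevant. If the real power is about half that, the result supports no such conclusion. The Discussion intends the results to serve the faculty's health-promotion goals and comparison with other universities, so the misreading would matter.

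**Working it through.** **Inputs.** From the Sample size section: control rate p1 = 0.40, α = 0.05, difference 10%, power 90%. From the Methods: n = 140 per arm. Sidedness and the scale of the 10% are not given, so both versions of each are tried. Normal quantiles: 1.960 (two-sided 5%), 1.645 (one-sided 5%), 1.282 (90% power).

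**1. Attempt to reproduce the plan's figure (90% power with 280).** Pooled-variance formula, with p̄ the mean of the two rates:

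n per arm = [z_α·√(2p̄(1−p̄)) + z_β·√(p1(1−p1) + p2(1−p2))]² / (p1−p2)²

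For 0.40 v 0.30, p̄ = 0.35, √(2 × 0.35 × 0.65) = 0.6745 and √(0.24 + 0.21) = 0.6708.

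- Two-sided: (1.960 × 0.6745 + 1.282 × 0.6708)² / 0.01 = 476.01, so **477 per arm (954 in total)**; 496 per arm with continuity correction.
- One-sided: 388 per arm; 408 with continuity correction.
- Relative 10%, 0.40 v 0.36, two-sided: 3,093 per arm.
- A rise, 0.40 v 0.50: 519 per arm two-sided, 423 one-sided.
- One-sample test against 40%, 90% power: 240 (two-sided) or 195 (one-sided) for 30%; 257 or 210 for 50%.
- The 2.5 added to the effect, 0.40 v 0.275, two-sided: 299 per arm.

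None of these gives 140 per arm or 280 in total at 90% power. The nearest is 281, but that is per arm, one-sided and at 80% power. The plan's figure is not reproduced.

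**2. Power that 140 per arm delivers.**

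Power = Φ{ [|p1−p2|·√n − z_α·√(2p̄(1−p̄))] / √(p1(1−p1) + p2(1−p2)) }

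For 0.40 v 0.30, two-sided: (0.10 × 11.832 − 1.960 × 0.6745) / 0.6708 = −0.207, and Φ(−0.207) = **0.418**.

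| Scenario | Two-sided | One-sided |
|---|---|---|
| 40% v 30% | 41.8% | 54.4% |
| 40% v 50% | 39.0% | 51.5% |
| 40% v 36% | 10.2% | 17.0% |

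For 40% v 30%, the unpooled formula gives 42.2% two-sided, and exact enumeration of the chi-square test gives 42.4% two-sided and 54.2% one-sided.

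**3. What 140 per arm can detect.** Two-sided 90% power is reached at a fall of about 18 points: for 40% v 22% the formula gives 90.7%.

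**4. Precision.** Wald 95% half-widths:

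- Difference: 1.96 × √(0.24/140 + 0.21/140) = 0.111, or ±11.1 points.
- One arm at 40%: 1.96 × √(0.24/140) = 0.081, or ±8.1 points.
- All 280 at 40%: 1.96 × √(0.24/280) = 0.057, or ±5.7 points.

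Conversely, ±2.5 points needs 1.96² × 0.24 / 0.025² ≈ 1,475 students for one prevalence, or 1.96² × 0.45 / 0.025² ≈ 2,766 per arm for the difference.

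**The case against.** **Other designs need fewer students.** All dependent variables are measured before and after, so a paired calculation is conceivable. A McNemar test of a 40% to 30% change at two-sided 5% and 90% power needs about 140 students if about 13.7% are discordant, or about 280 if about 27% are (both rates assumed). This does not rescue the text, because the stated difference is against the control group and no discordance is given. Adjustment for baseline would bring 477 down to 140 only with a correlation near 0.84, since 477 × (1 − 0.84²) ≈ 140. No such correlation or method is stated. For the same reason, a reader should not infer that adjustment will restore the power.

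**The trial is more than this one comparison.** This stands. The listed dependent variables are lifestyle changes, weight, body mass index, waist and hip; overweight/obesity prevalence is the sizing assumption. With Student's t test, 140 per arm has 90% power for a standardised difference of about 0.39, from (1.960 + 1.282) × √(2/140). The 42% describes the sizing scenario and not the whole trial.

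**The 2.5% may not be a half-width for the difference.** This also stands. Setting ±11 directly against 2.5 would treat an undefined quantity as defined. What can be said is that no confidence-interval reading tested matches it.

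**An article condenses the full protocol.** That excuses missing detail, not printed figures that conflict. It does dispose of one tempting inference, that 280 is defective for lacking an allowance for dropout: the article is silent on loss and speaks of follow-up only as under consideration, so this is no finding.

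**A reader might infer that the trial will more likely than not miss its target effect.** That holds for a two-sided test; one-sided power for 40% v 30% is 54%, and the article does not state sidedness. The shortfall from 90% remains either way.

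**Conclusion.** The point holds in this form: the stated inputs do not produce 280, and the 90% power is wrong as written for the comparison on which the trial was sized. For an absolute ten-point fall, power is about 42% two-sided or 54% one-sided; for a relative 10% it is about 10% two-sided or 17% one-sided. Ninety per cent power for 40% v 30% needs about 477 per arm two-sided, some 3.4 times the planned 140 (477/140). The 2.5% precision is undefined and fits none of the half-widths of ±11.1, ±8.1 and ±5.7 points.

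The calculation assumes an unadjusted comparison of overweight/obesity prevalence between independent arms at one time, with all 140 per arm analysed. The conclusion does not depend on sidedness, on whether the 10% is absolute or relative, or on the choice of variance formula. It makes no claim about power for the continuous outcomes. Because the stated power governs how a null result would be read, the paragraph must be corrected.

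**What to change.** Keep 280 and rewrite the Sample size paragraph:

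1. State whether the test is one- or two-sided and whether the 10% is absolute or relative. Only the sponsor can say which was meant.
2. Replace the 90% claim with the power delivered. If the answer is absolute and two-sided, suitable wording is: *With 140 students per arm and a two-sided 5% level, power is about 42% to detect a fall in overweight/obesity from 40% to 30%, and reaches 90% only for a fall to about 22%. The expected 95% confidence interval half-width for the difference is about ±11 percentage points.* For any other answer, take the matching figure from the table in the working.
3. Define the 2.5% precision so that it fits 280 students, or remove it.
4. Add that these figures describe the binary overweight/obesity comparison used for sizing and not the continuous outcomes.

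The cost is the rewording of one paragraph and a less favourable power statement. No participants are added, and neither the design nor the intervention changes.

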**Methods/design:**

We will carry out a randomized trial in a sample of 280 new undergraduate students at the National Autonomous University of Mexico’s Faculty of Higher Studies-Zaragoza (FES-Zaragoza, UNAM). There will be an experimental group (n = 140), comprising 20 students from each of the seven university departments (careers); these students will receive training as university student health promoters through an e-learning course. This course will allow the topics necessary for such promoters to be reviewed. There will be a control group (n = 140), comprising 20 students from each of the seven departments (careers); these students will not undergo the training. Later, the students who comply satisfactorily with the e-learning course will replicate the course to 10 of their classmates. A healthy-lifestyle questionnaire will be given to all the participants, and the parameters established in the self-care card will be recorded before and after the training. The study variables are as follows: (i) independent variable—compliance with the e-learning course; (ii) dependent variables—lifestyles changes prior to the educative intervention (including healthy eating, physical activity, and addiction prevention) and parameters related to health status established in self-care (including weight, body mass index, waist circumference, and hip circumference). Data will be analyzed using Student’s *t* test and logistic regression analysis odds ratios with 95% confidence intervals. The analysis of the open answers will be carried out with ATLAS. ti 5.5 software.

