Among the determining factors for adopting healthy lifestyles, it is necessary to examine gender, socioeconomic level, prior lifestyles, health status, the environment, parental lifestyles and health status, career choice, healthy support networks [24], and overall students’ knowledge about strategies to adopt healthy lifestyles during their time at university. Within this framework, the aim of the present study is to assess the impact of a training program to promote health among university students. Consequently, the trained university students will help create a safe, healthy learning environment at FES-Zaragoza, UNAM, which will in turn promote the development of an integrative health culture. At the same time, healthy lifestyles in terms of self-care will be promoted in the student community.

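### The only independent variable named is compliance with the course, not the randomised group; an analysis run on it as written would be open to self-selection

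*Protocol article*

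**What the plan says.** The Methods section states the design: "we will carry out a randomized trial using a sample of 280 new undergraduate students at FES-Zaragoza, UNAM". The experimental group is 140 students, 20 from each of seven departments, who take the e-learning course. For the others, "The control group (n = 140) will consist of 20 students from each of the seven departments (careers), but they will undergo no training". The Background gives the purpose: "the aim of the present study is to assess the impact of a training program to promote health among university students".

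The variables are listed in the Methods under the Sample size heading. The single independent variable there is "independent variable—compliance with the e-learning course for promoting health". The Abstract has the same definition: "independent variable—compliance with the e-learning course". The third class of variables (the intervenient ones) contains age, gender, pre-training health status and lifestyle, family income, academic course, and parental schooling and health. Randomised group is in none of the lists.

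The same Methods subsection later shows how the article uses the idea of complying: "the students who comply satisfactorily with the e-learning course will replicate the course to 10 of their classmates". The analysis text names Student's t test, logistic regression and Pearson's correlation, but not the groups to be compared. The only wording that points to a comparison between arms is in the sample-size paragraph, where the 10% difference is expressed in relation to the control group.

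**The concern.** The independent variable is the factor whose effect the analysis estimates. In a randomised trial that factor should be the allocation, because it is the only one that chance has balanced. Here the named factor is a behaviour that follows allocation and has no counterpart among controls, who are not offered the course.

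Anyone who follows the definition literally has to decide what to do with trained students who do not comply: drop them, pool them with the controls, or contrast them with the compliers. In each case one side of the comparison is selected by its own behaviour. The course has 20 topics (Table 1), and the Discussion says students fit it into their available time, so completion plausibly depends on motivation and existing habits. The Background lists prior lifestyle, health status and support networks as determinants of healthy lifestyles, and the same factors could influence who completes. Adjusting for the listed covariates may reduce the resulting confounding, but motivation is not among them and adjustment cannot restore what randomisation gave.

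At stake is whether the trial could report a benefit from a course that does nothing, and whether its main estimate answers the aim set out in the Background.

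**Working it through.** **Side by side.** The design is two randomised groups. The aim is the impact of the programme. The exposure is compliance, stated twice. Compliance in the article's own usage is satisfactory performance on the course, known only after allocation. The exposure therefore does not match the design or the aim, and nothing elsewhere in the article names allocation as the exposure.

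**Size.** The article gives no compliance rate and no prognostic difference between compliers and non-compliers, so there is no figure of the plan's own to reproduce. What follows is an illustration.

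Inputs from the article: 140 per group; 40% prevalence of overweight and obesity (Methods, Sample size).

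Inputs assumed:
- the course has no effect;
- a fraction *c* of the trained arm complies, 50–80%;
- the compliers' prevalence is *g* below the non-compliers', 5–15 percentage points;
- the post-training prevalence is compared without using baseline.

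Because randomisation makes the trained arm 40% overall:
- compliers: p_c = 0.40 − (1 − c)g
- non-compliers: p_n = 0.40 + cg

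With c = 0.60 and g = 0.10 there are 84 compliers and 56 non-compliers, with p_c = 0.40 − 0.40 × 0.10 = 0.36 and p_n = 0.46.
- Compliers v controls: 0.36 − 0.40 = −0.040.
- Compliers v everyone else: the rest have (140 × 0.40 + 56 × 0.46)/196 = (56 + 25.76)/196 = 0.417, so the difference is −0.057.
- Compliers v non-compliers: 0.36 − 0.46 = −0.10.
- Randomised groups: the trained arm has (84 × 0.36 + 56 × 0.46)/140 = (30.24 + 25.76)/140 = 0.40, so the difference is 0.

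The table gives the general formulas, the ends of the assumed range and the central case. Cells show the spurious benefit in percentage points and, in brackets, how often a two-sided 5% test of two proportions would reject.

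| Contrast | Bias | c = 0.8, g = 0.05 | c = 0.6, g = 0.10 | c = 0.5, g = 0.15 |
|---|---|---|---|---|
| Compliers v controls | (1 − c)g | 1.0 (5.3%) | 4.0 (9.0%) | 7.5 (18.0%) |
| Compliers v everyone else | 2(1 − c)g/(2 − c) | 1.7 (5.9%) | 5.7 (14.2%) | 10.0 (31.0%) |
| Compliers v non-compliers | g | 5.0 (8.0%) | 10.0 (22.0%) | 15.0 (44.0%) |
| Randomised groups | 0 | 0 (5%) | 0 (5%) | 0 (5%) |

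The first two contrasts therefore run from about 1 to 10 points. The contrast within the trained arm simply returns whatever gap was assumed.

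**Effect of baseline.** The article says all dependent variables are measured before and after training. If change from baseline is the outcome and the gap is wholly pre-existing and stable, it cancels and the bias is zero. What would remain is differential change, for example motivated students improving without the course. The article does not say how baseline values enter the analysis, so the table is an unadjusted case and the bias is smaller to the extent that baseline is used.

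**The case against.** The strongest reply is that no complier comparison is actually planned. The tests are not tied to any groups. No sentence says non-compliers are dropped, pooled or contrasted. The surrounding text points to the arms: two groups defined by receiving or not receiving training, a target difference set against the control group, and a questionnaire for all participants. On this reading, compliance is loose wording for having been given the course, and the phrase about complying satisfactorily only selects who goes on to teach classmates.

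Much of this stands. A reader might infer that the trial has committed itself to a self-selected analysis. The article does not support that, because it leaves the compared groups unnamed and does not exclude a comparison by arm. It is also not supported to call the course voluntary: the article says that experimental students receive it and is silent on whether completion is optional.

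What does not stand is that the point can be left to a fuller document. The exposure is not an omitted detail. It is stated, twice, and it is the wrong variable for the design. If loose wording is the explanation, the same two sentences still need correcting.

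The numbers are also open to challenge. The compliance rates and gaps are not anchored in the article. Overweight prevalence is the quantity used for sample size, whereas the health-status outcomes listed are weight, body mass index and waist and hip circumference. It is tempting to express the bias as a share of the 10% target difference, but the article does not say whether that 10% is absolute or relative, so no such share is given here.

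**Conclusion.** The point holds in conditional form. The article names a post-allocation behaviour, observable in one arm only, as the sole independent variable of a randomised trial, and nowhere states a comparison by randomised group. Run as written, the analysis would be open to self-selection and would not estimate the impact of the programme.

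This rests on the text and needs no assumed number. The size does: about 1 to 10 points of spurious benefit against controls or everyone else, given no course effect, 40% prevalence, 50–80% compliance, a 5–15 point gap and no baseline adjustment, and less if change from baseline is analysed. These figures show that the error can matter. They do not predict the bias in this trial.

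**What to change.** In the Abstract and in the Methods list of variables, name the randomised group (experimental v control) as the independent variable. Add that every randomised student is analysed in the group allocated, whether or not the course was completed. Keep compliance only as a secondary, exploratory variable, labelled as a non-randomised comparison.

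An estimate of the effect in compliers that uses allocation as an instrument is not recommended as a routine addition. Trained students are to repeat the course for 10 classmates, controls come from the same departments and are not excluded from this teaching, and such spillover would undermine the no-interference assumption that the method needs.

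The cost is a change to two sentences and one added statement. The downside is that the as-randomised estimate will usually be smaller than a complier contrast. For example, if a true 10-point effect occurred only in compliers, 50–80% compliance (assumed) would give 0.5 × 10 = 5 to 0.8 × 10 = 8 points between the arms.

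### The article names only single-time-point or before/after tests for a design with baseline, post-course and possibly 4 to 8 further visits, fixes no analysis visit, and leaves baseline out of the between-arm comparison of continuous outcomes

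*Protocol article*

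**What the plan says.** Everything relevant stands in the Methods, under the heading Sample size.

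- **Firm measurement plan:** "All dependent variables will be measured prior to and after the educative intervention". The outcomes are weight, body mass index, waist and hip circumference, and lifestyle measures.
- **Longer schedule, stated tentatively:** "We are considering a follow-up every 6 and 12 months during 4 years". This sentence directly follows the one about trained students passing the course on to classmates. It does not say which students are followed or for which outcomes.
- **Analysis:** "Results will be analyzed using Student’s *t* test and logistic regression analysis odds ratios with 95% confidence intervals". Pearson's correlations and a 0.05 threshold complete the list. The Abstract repeats the t test and logistic regression.

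Health status and lifestyle before training are listed among the intervening variables, but the article does not say that they enter any model. It also does not say whether the t test is paired, which visit decides the comparison, or how several records from one student are handled.

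**The concern.** The design and the analysis are described in adjacent paragraphs and do not match. An unpaired t test, ordinary logistic regression and Pearson's correlation each need one independent record per student. A paired t test deals with one before/after pair within an arm. It does not compare the randomised arms, and it does not extend to 4 or 8 visits.

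Two things are at stake. First, if the long follow-up happens, nothing in the text steers the analyst towards a valid use of these tests. Stacking visits would understate standard errors. Testing each visit at 0.05 would multiply the chances of a positive result, and each test would use only the students who attended. Second, even if only the before/after measurement happens, a t test between arms on post-course values makes no use of the baseline value, so precision that costs nothing is lost.

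**Working it through.** **Inputs from the article:** 280 students, 140 per arm; follow-up over 4 years at 6 and 12 months; threshold p<0.05. **Assumed, because the article gives no figure:** the within-student correlation ρ, shown over 0.3–0.9 and taken as equal between all visits. The article gives no figure of its own on this point to reproduce.

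**1. Number of follow-up visits.** 48 months / 6 = 8. 48 months / 12 = 4. Both readings are carried forward. Baseline and the post-course measurement are not counted.

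**2. If visits were pooled as independent records.** The variance of the arm difference is understated by the design effect DE = 1 + (m − 1)ρ, where m is the number of visits. The true type I error of a nominal two-sided 5% test is 2 × [1 − Φ(1.96/√DE)].

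| ρ | DE, m = 4 | Type I error, m = 4 | DE, m = 8 | Type I error, m = 8 |
|---|---|---|---|---|
| 0.3 | 1.9 | 16% | 3.1 | 27% |
| 0.5 | 2.5 | 22% | 4.5 | 36% |
| 0.7 | 3.1 | 27% | 5.9 | 42% |
| 0.9 | 3.7 | 31% | 7.3 | 47% |

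A simulation of the pooled t test (140 per arm, 8 visits, 4,000 replicates) gave 36%, 42% and 48% for ρ = 0.5, 0.7 and 0.9, in agreement with the formula.

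**3. If 8 visits were tested separately at p<0.05.** With equally correlated test statistics under no effect, the simulated chance of at least one significant result is 25% (ρ = 0.5), 19% (ρ = 0.7) and 12% (ρ = 0.9). These figures are for full attendance.

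**4. What baseline adjustment gains in the before/after case.** Take equal variances before and after, with post-course variance 1. The variance of the arm contrast is then proportional to:

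- post-course values only: 1
- change scores: 2(1 − ρ)
- ANCOVA: 1 − ρ²

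At ρ = 0.5 these are 1, 1.00 and 0.75. At ρ = 0.7 they are 1, 0.60 and 0.51. At ρ = 0.9 they are 1, 0.20 and 0.19. ANCOVA is never worse than either t test. Its gain over change scores is modest when ρ is high, and its gain over post-course values is large.

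**The case against.** The strongest reply is that the article describes no invalid analysis.

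- The long follow-up is only under consideration, and the firm plan is before and after. For that plan, a t test on post-course values or change scores, or a logistic model of post-course status, uses one value per student and is valid. So is a test at one chosen later visit. **This stands.**
- A reader might infer that the reported p-values will be wrong because visits are treated as separate students. No sentence says that visits will be pooled, and the type I error figures apply only if they are. **This stands.**
- A reader might also infer that follow-up certainly produces eight records per student. The wording equally allows four. **This stands.**
- A reader might attribute low power to testing only the students who attend. For 40% v 30%, two-sided, full attendance of 140 per arm gives Φ[(0.10 − 1.96 × √(2 × 0.35 × 0.65/140)) / √((0.24 + 0.21)/140)] = Φ(−0.21) = 42%, against the stated 90%. That shortfall is a separate sample-size matter, and the article gives no drop-out rate from which to calculate a further loss.
- An article condenses, and a fuller document may hold the longitudinal model. **This stands in part.** The article does not leave the analysis open: it names its methods twice, and the named t test is what can be improved.

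**Conclusion.** The point holds as a mismatch between the named tests and the design, and as an inexpensive improvement. It is not a demonstrated error in a planned result. No named method models more than two records per student, no analysis visit is fixed, and the t test compares continuous outcomes between arms without the baseline value.

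The inflation in steps 2 and 3 is conditional on how the tests are applied, on an assumed common correlation and, for step 3, on the 8-visit reading. Under the annual reading and the lowest correlation tried, pooling would still roughly triple the nominal 5%. The case for baseline adjustment does not depend on the long follow-up taking place. The documents do not support a claim that visits will be pooled, or that drop-out is the main cause of low power.

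**What to change.** Replace the t test as the main between-arm analysis:

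- **Continuous outcomes (weight, body mass index, waist, hip, lifestyle scores):** a linear mixed model with randomised group, visit, group × visit and baseline value, with student as the repeated unit.
- **Overweight/obesity:** GEE or mixed logistic regression with the same structure.
- **Population and contrast:** all randomised students with all available visits, and the primary contrast at one visit chosen in advance.
- **If only the before/after measurement goes ahead:** the baseline-adjusted comparison (ANCOVA) in place of the t test.

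The text should also state whether follow-up is six-monthly or annual. The change is to wording only and uses data already planned, with no extra students or visits. The downside is a slightly more complex model to fit and report.

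### Every outcome has a baseline value, but the only method named for comparing means is a t test, which cannot adjust for it; between-arm ANCOVA is at least as precise on either between-arm reading

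*Protocol article*

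**What the plan says.** All of the relevant text is in the Methods section of the protocol article, mostly under the Sample size heading.

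- Design: "we will carry out a randomized trial using a sample of 280 new undergraduate students at FES-Zaragoza, UNAM", split into two groups of 140.
- Lifestyle outcomes, as the article words them: "dependent variables—lifestyles changes prior to the educative intervention (including healthy eating, physical activity, and addiction prevention".
- Body measurements, as the article words them: "parameters related to health status in self-care (including weight, body mass index, waist circumference, and hip circumference".
- Timing: "All dependent variables will be measured prior to and after the educative intervention".
- Pre-training variables: the article lists "intervenient variables—age, gender, health status before training, current lifestyle (before training), family income, academic course, parents’ schooling, and parents’ health status". It does not say which analysis uses them.
- Analysis: "Results will be analyzed using Student’s *t* test and logistic regression analysis odds ratios with 95% confidence intervals". The only other inferential tool named is Pearson correlation.
- Sizing: the starting point is a 40% prevalence of overweight and obesity taken from unpublished work, and the remaining inputs read "We considered a significance level of 5%, a difference in clinical interest of 10% related to the control group, and a precision of 2.5" (a percentage). The power stated is 90%. No before-after correlation enters this calculation.

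**The concern.** Weight, BMI, waist, hip and the lifestyle measures are recorded at baseline for every student. Where baseline and follow-up are correlated, part of the variation between students at follow-up is already known at entry, and a model containing the baseline value removes it from the error. A t test on post-training values discards that information. A t test on change uses it, but subtracts the full baseline whatever the correlation, which adds noise when the correlation is low.

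The wording also admits a third reading, a paired before-after test within each arm. That would not be a comparison between randomised groups, because it mixes any effect of the course with the ordinary change of students starting university.

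At stake is the precision of the between-arm comparison, in a trial whose size gives much less than the power it states for its own sizing outcome.

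**Working it through.** **Inputs from the article.** 140 per arm; significance level 5% (taken as two-sided, since sidedness is not stated); power 90%; 40% overweight/obesity; difference 10% (taken as 40% versus 30%, since the article does not say whether it is absolute or relative).

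**Assumed inputs.** The before-after correlation r, shown from 0.3 to 0.95. Equal SD before and after and in both arms; no dropout.

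**Step 1: the plan's own figure.** For 40% versus 30%, the pooled proportion is 0.35 and

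n per arm = [1.960·√(2·0.35·0.65) + 1.2816·√(0.4·0.6 + 0.3·0.7)]² / 0.10² = (1.3221 + 0.8597)² / 0.01 ≈ 476.0, rounded up to 477 per arm, or 954 in total.

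The stated 280 is not reproduced. With 140 per arm, power is Φ[(0.10·√140 − 1.3221)/0.6708] = Φ(−0.207) ≈ 0.42. This is a separate problem. It matters here because it shows how little precision there is to spare.

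**Step 2: continuous outcomes.** The variance factor, relative to a post-value t test, is:

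- post-value t test: 1
- change-score t test: 2(1 − r)
- ANCOVA: 1 − r²

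Since 1 − r² = (1 − r)(1 + r) and 1 + r ≤ 2, ANCOVA is never less precise than the change score. Since r² ≥ 0, it is never less precise than the post value (apart from the one degree of freedom spent on the baseline term, negligible at 280).

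Detectable difference in SD units = (1.960 + 1.2816)·√(2/140)·√factor = 0.387·√factor.

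| r (assumed) | Post value | Change score | ANCOVA | ANCOVA variance / post value | ANCOVA variance / change score |
|---|---|---|---|---|---|
| 0.3 | 0.387 | 0.458 | 0.370 | 0.91 | 0.65 |
| 0.5 | 0.387 | 0.387 | 0.336 | 0.75 | 0.75 |
| 0.7 | 0.387 | 0.300 | 0.277 | 0.51 | 0.85 |
| 0.8 | 0.387 | 0.245 | 0.232 | 0.36 | 0.90 |
| 0.9 | 0.387 | 0.173 | 0.169 | 0.19 | 0.95 |
| 0.95 | 0.387 | 0.123 | 0.121 | 0.10 | 0.975 |

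Against a post-value test, ANCOVA saves more than half the variance only when r² > 0.5, that is r above about 0.71. Against a change-score test it saves 10% at r = 0.8 and 5% at r = 0.9.

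**Step 3: overweight/obesity.** Simulated trials with 140 per arm; normal BMI before and after with correlation r; follow-up BMI in the trained arm shifted so that the proportion above the cut-off falls from 40% to 30% (0.271 SD, from the normal quantiles for 60% and 70%); a two-sided 5% test of group in a logistic model.

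| Model | Power |
|---|---|
| Group only | about 0.43 (analytic 0.42) |
| Group + baseline BMI, r = 0.5 | about 0.48 |
| Group + baseline BMI, r = 0.8 | about 0.65 |
| Group + baseline BMI, r = 0.9 | about 0.76 |

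Repeat runs of 1,000 to 4,000 trials scatter by up to about 0.03 around these values: 0.46 to 0.48, 0.63 to 0.66 and 0.75 to 0.79 for the adjusted models. No run reaches 0.90.

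**The case against.** There are four objections.

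1. *The article is condensed and a fuller plan may exist.* Which t test is used, and which covariates enter the logistic model, may fairly be left to that plan, and their absence is not the point. What stands is that the article does name a method for comparing means, and that a better one exists on either between-arm reading of it.

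2. *The plan does not ignore baseline.* A reader might infer that baseline is never used as a covariate. The text does not support that. It lists pre-training health status and lifestyle as intervenient variables and leaves the logistic covariates open. The gain in Step 3 therefore applies only if baseline BMI would otherwise have been left out.

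3. *The loss may be small.* A reader might infer that most of the available precision is thrown away. That holds only for a post-value test with r above about 0.71. The article words the lifestyle outcomes as changes, and a between-arm t test on change is a natural use of before-after data; at high correlations it is almost as good as ANCOVA. At low correlations, plausible for questionnaire outcomes and for follow-up planned over 4 years, adjustment gains little over a post-value test. All of this stands.

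4. *A t test is not wrong.* A between-arm t test on post values or on change is valid in a randomised trial. This stands too: for both, the issue is efficiency, not bias. The within-arm test would raise a question of validity, but the article does not say that it will be used, so it cannot be charged with it.

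**Conclusion.** The point holds as one of efficiency and specification. Baseline is collected for every outcome, the only method named for means cannot adjust for it, and no analysis is tied to the listed pre-training variables. ANCOVA is at least as precise as both between-arm t tests at every correlation.

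The size of the gain depends on two things that the article does not give: the correlation and the type of t test. It runs from slight (0.387 to 0.370 SD against post values at r = 0.3; 0.173 to 0.169 SD against change at r = 0.9) to large (0.387 to 0.169 SD against post values at r = 0.9). One practical advantage does not depend on knowing r: ANCOVA removes the need to guess which of the two t tests will turn out better.

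For overweight/obesity, baseline BMI adds roughly 0.05 to 0.33 to a power of about 0.43 over r = 0.5 to 0.9, if the model would otherwise omit it. It does not repair the sample size. The revision is worth making, but nothing here shows that the planned between-arm comparison would be biased.

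**What to change.** 1. Replace Student's t test by between-arm ANCOVA for the continuous outcomes: follow-up value on randomised group plus the baseline value of the same variable.
2. For overweight/obesity, use logistic regression on randomised group plus baseline BMI. Beside the odds ratio, report the standardised risk difference with its 95% confidence interval, because the target effect is stated as a 10% difference.
3. State that any within-arm before-after tests are descriptive only.

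The cost is a change of analysis wording. The baseline data are already planned, and ANCOVA and logistic regression are standard procedures in the software named. The standardised risk difference needs a short further calculation from the fitted probabilities. No extra students or visits are needed. The shortfall in sample size has to be dealt with separately.
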